## Secondary outcomes

**Repeatability/reproducibility:** Outcome metrics will be the repeatability and reproducibility of measurements (identification and thickness) of structural parameters of the cornea, corneal surface contour and refractive power.

**Sensitivity and specificity:** We will use published grading systems specific to the two main conditions of FECD and keratoconus. For keratoconus, the sensitivity of the LiveOCT will be assessed by its ability to detect the same diagnostic parameters of non-uniform and focal corneal thinning and irregular and non-asymmetric anterior and posterior corneal profiles currently measured using the Pentacam. For FECD, the sensitivity of the LiveOCT will be assessed by its ability to measure increases in corneal thickness and areas of corneal swelling, and excrescences (guttata) and thickening of Descemet's membrane in patients who have guttata evident with slit lamp bio microscopy and increased corneal thickness measured with the Pentacam. Specificity will be defined as the percentage in which the described diagnostic changes in the cornea for keratoconus and FECD are not apparent with the LiveOCT device.

**Patient experience:** Study participants will be asked to fill in a simple set of questions concerning their experience with the LiveOCT devices. The patients will be asked to fill out paper copies of the questionnaire after the end of each study appointment, but the study nurse will be available to help if required.

If the participant indicates that they are feeling particularly anxious or depressed on the questionnaire, a member of their care team will pass this information onto their GP.

**Cost Effectiveness:** See 13.3 - economic evaluation

1. Definition of end of study

The study will be completed and terminated on 31st October 2022, which is defined to be the date when analysis of the data collected during the trial is being completed.

Suspension or early termination of the study when there are serious concerns about subjects’ safety and inadequate performance, that cannot be mitigated by modifications of the study protocol based upon the review of the safety data.

1. Discontinuation/ withdrawal of participants from study treatment

If a decision is made by the participant and or/clinician not to continue with the study, the participant will be removed from it and the event recorded. Data will still be collected unless the participant explicitly withdraws consent for it.

1. Statistics and data analysis

## Sample size calculation

The current gold standard for measuring the cornea is based on the tomographic images of the Pentacam for the thinnest corneal thickness (TCT). There is insufficient evidence in the literature to determine what change might occur in Bowman’s layer longitudinally. Bowman’s layer has not been measured before using a Pentacam so that we do not have a comparison. The primary endpoint, therefore, is a change in TCT. We do not know whether the change in TCT will be reflected in a change in Bowman’s layer and or Descemet’s membrane thickness and therefore we are not able to use the changes in these layers to determine the sample sizes. The changes in Bowman’s layer and Descemet’s membrane will be exploratory but we expect that changes will occur as TCT changes. For TCT, using a Pentacam, the cut-off for a change in TCT is 12.1um between the mean of three measurements on 2 occasions (Brunner et al, 2018). We expect the LiveOCT to detect all patients who have this change, that is, >12.1um in TCT. The incidence of patients with keratoconus (KC) changing over a 6 month period is expected to be 20% using the Pentacam. Therefore 8 of the 40 patients included will be expected to show this change using the Pentacam. Based on the increased resolution of the Liverpool LiveOCT we expect a much greater sensitivity for detecting change in TCT. We estimate that 50% of patients will show a change that we can detect based on the increased resolution of 2μm of the LiveOCT compared to 20μm of the Pentacam. Evidence for the current OCT performed worse than the Pentacam (Brunner et al) hence the choice of the Pentacam as a comparison for TCT. A difference, therefore, of between 20% and 50% would require a sample size of 36 with an alpha of 0.05 and beta 0.2. Given that over the course of the study 10% will drop out we calculate a sample size of 40 patients with KC. For patients with FECD, we do not have data on the change in TCT, however, extrapolating from patients with KC the change in TCT is usually greater in FECD hence a similar or slightly smaller sample size is needed which we estimate to be 30 patients. For healthy subjects we do not expect the change in TCT to be greater than the 95% TCT cut-off 8.81um (Pentacam) over the course of the study, based on Brunner et al 2018. We, therefore, expect 20 subjects in this group to provide reproducibility data using the LiveOCT.

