[20 Dissemination and intellectual property 18](#_Toc86830258)

[References 19](#_Toc86830259)

List of abbreviations

ADE Adverse Device Effect

AE Adverse Event

CERC Clinical Eye Research Centre

CRF Case Report Form

ECD Endothelial cell count

FMEA Failure Modes and Effects Analysis

GCP Good Clinical Practice

FECD Fuch’s Endothelial Corneal Dystrophy

LIVE-OCT Liverpool Optical Coherence Tomography

LUHFT Liverpool University Hospitals NHS Foundation Trust

OCT Optical Coherence Tomography

PIS Patient Information sheet

REC Research Ethics Committee

SADE Serious Adverse Device Effects

SAE Serious Adverse Event

SPEU St Paul’s Eye Unit

UoL University of Liverpool

USADE Unanticipated Serious Adverse Device Effect

1. Study summary

| Study Title | Clinical Evaluation of a Novel LiveOCT Device to Improve the Management of Eye Disease | |
| --- | --- | --- |
| Internal ref. no. (or short title) | LiveOCT Study | |
| Clinical Phase | Na | |
| Study Design | Prospective Observational Study | |
| Study Participants | Patients aged 12 years and above with a diagnosis of either keratoconus or Fuchs endothelial corneal dystrophy (FECD) and/ or corneal lamellar surgery and subjects with no corneal disease (healthy volunteers). | |
| Planned Sample Size | 40 patients with keratoconus, 30 with FECD and/or corneal lamellar surgery, and 20 with no known corneal abnormalities (healthy volunteers). | |
| Treatment duration | N/A | |
| Follow up duration | Baseline and follow up 3 months and 6 months | |
| Planned Study Period | *1^st^ May 2021 to 30^th^ Oct 2022* | |
|  | Objectives | Outcome Measures |
| Primary | To compare image quality | The quality of the LiveOCT images from 2 variants (D1 and D2) will be compared with the existing models according to predefined diagnostic image criteria. |
| Secondary | To assess repeatability of image quality  Sensitivity  Assess cost effectiveness  Patient experience |  |
| Medical device | Liverpool Optical Coherence Tomography device (LiveOCT). | |
| Formulation, Dose, Route of Administration | Na | |

1. Background

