## Objectives

### Primary objective

- To compare the quality and information provided of corneal images obtained with the new LiveOCT device variants (D1 and D2) with those obtained using standard clinical instruments including existing OCT devices.

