## Primary outcomes

**Image quality**: The quality of the LiveOCT images will be compared with the existing models according to predefined diagnostic image criteria.

**Added information:** The anticipated additional information provided by our LiveOCT will then be used to determine if and what changes have occurred in the patients with FECD and keratoconus that were not apparent with the standard tests and whether these changes reflect or indicate change (deterioration or improvement) in the status of the disease. We will also determine which additional components of the cornea have been affected and whether and to what extent are the features reproducible. An evaluation will also be undertaken to determine whether the information provided by our LiveOCT is associated with specific features evident in the images from the standard instruments and whether the information is new or redundant.

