**Micro-costing analysis**

We will undertake a micro-costing of the introduction of the LiveOCT device into clinic based on our previous use of micro-costing. We will explore what there is to be learnt from recent developments in micro-costing in health economics and in time-driven activity-based costing as part of the value-based health care movement.

In order to undertake our cost-consequence analysis we will collect data at baseline, 3 and 6 months. See table 2.

**Table 2:** Draft plan for preliminary health economics data collection

| **No.** | **Data** | **Details** |
| --- | --- | --- |
| **Intervention delivery data** | | |
| 1. | Staff | Type of staff (i.e. type of healthcare professional), number & grade of staff who prepare, conduct the imaging, analyse scan, provide feedback to patients regarding scan and present in the imaging room for each patient’s OCT imaging appointment for both standard and new OCT imaging at each study time-point. |
| 2. | Duration of time taken for… | Preparatory, administration, conducting the imaging, analysis of the scan and feeding back to patients regarding scan for each patient’s OCT imaging appointment for both standard and LiveOCT imaging at each study time-point. |
| 3. | Disposable items | What are the disposable items and total quantity of each item for both standard and new OCT imaging? |
| 4. | Overheads | What are the relevant overheads to be charged for the department/hospital for both standard and new OCT imaging? |
| **Outcome measures -** | | |
| 5. | Primary - Quality corneal images score | What is the score of quality corneal images for each patient’s corneal image produced by standard OCT device and LiveOCT device at each study time-point? |
| 6. | Secondary – Patient’s experience, staff experience | We are aware that the main clinical study is collecting data on these. |

We will undertake deterministic sensitivity analysis to explore implications of for example various costs of the LiveOCT device and any time and motion implications of any additional time in clinic taken relating to the introduction of the LiveOCT device.

1. Data management

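### The sample-size section names change in thinnest corneal thickness as the primary endpoint, but the summary, objectives and outcomes make image quality primary, so the stated power does not belong to the declared primary outcome

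*Protocol*

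**What the plan says.** The sample-size section of the protocol reasons that layer-specific changes cannot be used for sizing, and concludes: "The primary endpoint, therefore, is a change in TCT". It treats changes in Bowman's layer and Descemet's membrane as exploratory. It then compares the share of keratoconus patients in whom a TCT change is detected over 6 months: 20% by Pentacam and 50% by LiveOCT. This leads to 36 patients, or 40 after 10% dropout. The figure of 30 for Fuchs dystrophy is extrapolated from the same TCT argument.

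The other places that name a primary say something else:

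- Study summary, primary objective: "To compare image quality".
- Primary outcomes, first item: "The quality of the LiveOCT images will be compared with the existing models according to predefined diagnostic image criteria".
- Primary outcomes, second item (added information): "The anticipated additional information provided by our LiveOCT will then be used to determine if and what changes have occurred".
- Table 2 of the economic evaluation: "Primary - Quality corneal images score".

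The Primary objective section likewise asks about the quality of the images and the information they provide, for both variants (D1 and D2) against standard instruments.

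The nearest secondary outcomes are "repeatability and reproducibility of measurements (identification and thickness) of structural parameters of the cornea" and, for keratoconus sensitivity, the device's "ability to detect the same diagnostic parameters of non-uniform and focal corneal thinning". For Fuchs dystrophy there is also detection of increased corneal thickness.

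**The concern.** A reader of the current protocol finds two different answers to the question of what the primary endpoint is. The only alpha, power and sample size belong to an endpoint that no outcome section lists, while the endpoint that four places call primary has no sample-size basis.

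Two things are at stake. First, a report that presents image quality as the primary result and cites the protocol's 80% power would be claiming power that was never calculated for it. Second, with two sets of primaries on paper, a result on TCT change, on image quality or on added information could each be presented as primary after the data are seen.

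**Working it through.** **Step 1. Does the sample size come from the TCT endpoint?**

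Inputs, all from the sample-size section: detection rates 0.20 (Pentacam) and 0.50 (LiveOCT), alpha 0.05, beta 0.2, dropout 10%. The section does not say whether alpha is one- or two-sided; I take two-sided.

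Two independent proportions, unpooled variance:

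n = (z for alpha/2 + z for power)² × [p1(1−p1) + p2(1−p2)] / (p2−p1)²

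= (1.960 + 0.842)² × (0.16 + 0.25) / 0.30² = 35.76, rounded up to 36.

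Dropout: 36 / (1 − 0.10) = 40.

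Both stated figures reproduce. Other common formulas give nearby values (39 with pooled variance, two-sided; 37 one-sided with continuity correction), but the unpooled two-sided form gives exactly 36. I use it only to trace the figure. Each patient is measured on both devices, so a paired calculation would differ; that is a separate matter and is not judged here.

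**Step 2. Is there any sizing for image quality?**

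The sample-size section gives no expected score, difference, standard deviation, success rate or margin for image quality. No power for it can be calculated from the protocol, in either direction.

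**Step 3. Where is each candidate named as primary?**

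| Place | Image quality | Added information | Change in TCT |
|---|---|---|---|
| Study summary | yes | no | no |
| Primary objective | yes | yes | no |
| Primary outcomes | yes | yes | no |
| Table 2 (economic evaluation) | yes | no | no |
| Sample size calculation | no | no | yes |

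TCT is named only in the sample-size section. The secondary outcomes cover repeatability of thickness measurements, detection of focal thinning, and increased thickness in Fuchs dystrophy. None is a change over time in TCT, or the share of patients beyond a change cut-off such as the 12.1 µm that the sample-size section gives for the Pentacam.

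**Step 4. What would splitting alpha between D1 and D2 cost?**

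This bears on the fix, because the sizing refers to LiveOCT as one device with one alpha. With the formula of step 1 and two-sided alpha 0.025 (z = 2.241):

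n = (2.241 + 0.842)² × 0.41 / 0.09 = 43.3, so 44 evaluable; 44 / 0.9 = 48.9, so 49 recruited.

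Power with 36 evaluable: √(36 × 0.09 / 0.41) − 2.241 = 2.811 − 2.241 = 0.570, which corresponds to about 72%.

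**The case against.** The best defence is that TCT serves only as a measurable stand-in for sizing, in a proof-of-concept observational study whose real question is image quality. That is a reasonable design, but it is not what the text says: the section calls TCT change the primary endpoint and ranks the layer changes below it as exploratory. Nor can a separate analysis plan settle this, since the conflict lies between two statements of the protocol itself.

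A second defence stands in part. The added-information outcome asks about changes in keratoconus and Fuchs dystrophy that the standard tests did not show. A TCT change seen by LiveOCT and missed by the Pentacam could loosely be one such change. A reader might infer that the stated power applies to none of the primary outcomes; that goes too far. What can be said is that it does not apply to image quality, and that the added-information text names neither TCT, a cut-off nor a proportion.

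Three further inferences are tempting and not supported:

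- *The comparators contradict each other (Pentacam against existing OCT).* The primary outcome speaks of existing models without restricting them to OCT, and the primary objective refers to standard clinical instruments, which can include the Pentacam. The sample-size section also explains its choice of the Pentacam for TCT.
- *The protocol omits the test for 20% against 50%.* Its analysis section is explicitly illustrative, and this detail is commonly left to an analysis plan.
- *Testing D1 and D2 inflates the family-wise error.* The protocol does not say that each variant will be tested confirmatorily, handling of multiplicity can sit in the analysis plan, and any figure would need a correlation that the document does not give. It would not measure the endpoint conflict in any case.

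**Conclusion.** The concern holds as a contradiction over which endpoint is primary. The sample-size section declares change in TCT primary and takes its keratoconus and Fuchs dystrophy numbers from it; four other places declare image quality primary, two of them together with added information. The 36 and 40 follow from the TCT inputs alone, assuming a two-sided alpha and the unpaired, unpooled formula.

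The consequence is qualitative. The stated 80% power does not belong to image quality, and the power for image quality is unknown rather than shown to be low. The finding rests on the current wording only and needs no outside figure. It should be corrected before any result is labelled primary.

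**What to change.** Amend the wording so that one primary stands throughout. Either option resolves the conflict.

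**(a) Keep image quality primary.** In the sample-size section, replace the sentence that declares TCT the primary endpoint with a statement that the sample size is based on change in TCT in keratoconus, LiveOCT against Pentacam, baseline to month 6. List that measure as a named secondary outcome. State that 40/30/20 was not powered on image quality. This touches the fewer sections.

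**(b) Make TCT change primary.** Put the proportion of keratoconus patients with a TCT change from baseline to month 6, LiveOCT against Pentacam, as the primary in the summary, primary objective, primary outcomes and sample-size section, and align the primary label in Table 2. Move image quality and added information to secondary. The protocol gives change cut-offs for the Pentacam only, so the LiveOCT cut-off must be fixed before the comparison is analysed.

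Under either option, name D1 or D2 as the variant in the powered comparison, so that the single alpha of 0.05 stands. If both are to be tested at 0.025 instead, restate the power: about 72% with 36 evaluable patients by the protocol's own formula. Holding 80% would take 44 evaluable (49 recruited), which is no longer a wording change.

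Cost: a protocol amendment, with no change to visits, scans or enrolment as long as the recruitment target stays at 40. The downside of (a) is that the declared primary must be described as unpowered; that of (b) is that the outcome now named primary in four places is demoted.

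### LiveOCT has no change cut-off of its own, and the 50% that sizes the keratoconus group rests on optical resolution rather than on measurement error

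*Protocol*

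**What the plan says.** All of the following is in the protocol's Sample size calculation (section 13.1) unless stated otherwise.

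- The section takes the Pentacam as the reference for TCT and names change in TCT as the primary endpoint.
- Pentacam change has an empirical definition: "the cut-off for a change in TCT is 12.1um between the mean of three measurements on 2 occasions".
- The Pentacam rate is given as follows: "The incidence of patients with keratoconus (KC) changing over a 6 month period is expected to be 20% using the Pentacam".
- For LiveOCT, "We expect the LiveOCT to detect all patients who have this change, that is, >12.1um in TCT". The rate beyond that is argued from optics: "We estimate that 50% of patients will show a change that we can detect based on the increased resolution of" 2 µm "of the LiveOCT compared to 20μm of the Pentacam". The section presents this as a large gain in sensitivity. It states no LiveOCT cut-off in µm and no LiveOCT test-retest SD.
- The 20% against 50% contrast "would require a sample size of 36 with an alpha of 0.05 and beta 0.2", and allowing that "10% will drop out we calculate a sample size of 40 patients with KC".
- Healthy volunteers are expected to stay within a Pentacam limit of 8.81 µm, and "We, therefore, expect 20 subjects in this group to provide reproducibility data using the LiveOCT".

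Elsewhere, Study design and Baseline and subsequent assessments schedule three measurements per device at each visit. Secondary outcomes lists repeatability and reproducibility, and defines specificity by the absence of diagnostic features of keratoconus and FECD. Statistical analysis plan (13.2) names Bland-Altman plots, coefficients of variation, a random-effects model and sensitivity and specificity tests.

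**The concern.** One paragraph holds the two devices to different standards. A Pentacam change must exceed a limit derived from repeated measurements. A LiveOCT change is whatever finer resolution is expected to reveal.

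Resolution describes how close two structures can lie and still be separated in an image. Whether a difference between two visits is real depends on how far the visit means vary when nothing has changed. That is a matter of repeat error, which includes repositioning, segmentation and day-to-day variation.

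Without a LiveOCT limit set on the same basis, the device with more noise or a laxer threshold flags more patients. A result of 50% against 20% could then be reported as better sensitivity when some or all of the excess is error. The planned specificity does not guard against this, because it concerns diagnostic features and not false detection of change over time.

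**Working it through.** **1. The plan's own figure.** Inputs: 20%, 50%, alpha 0.05 (taken as two-sided), beta 0.2, dropout 10%. For two independent proportions with unpooled variance:

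n = (1.960 + 0.842)² × (0.2×0.8 + 0.5×0.5) / 0.30² = 7.849 × 0.41 / 0.09 = 35.8, so 36. Then 36 / 0.90 = 40.

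Both figures reproduce. The difficulty lies in the 50% input, not in the arithmetic. (The formula treats the devices as separate groups although the same patients have both. That is a different matter and is not pursued here.)

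**2. Does resolution set detectable change?** On the protocol's figures the Pentacam resolves 20 µm but has a change cut-off of 12.1 µm, a ratio of 12.1/20 = 0.6. Its detectable change is below its resolution, so the tenfold gain in resolution (20/2) says nothing definite about LiveOCT's detectable change.

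**3. How many stable eyes would be flagged?** The protocol gives neither a LiveOCT cut-off nor an SD, so both are assumed. With normal error, the flagged rate is 2 × [1 − Φ(c / SD)], where c is the cut-off and SD is that of the difference between two visit means in an unchanged eye.

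| SD of difference (µm) | c = 2 µm | c = 4 µm | c = 6 µm |
|---|---|---|---|
| 1.02 | 5% | <0.1% | <0.1% |
| 2 | 32% | 5% | 0.3% |
| 2.25 | 37% | 8% | 0.8% |
| 2.97 | 50% | 18% | 4% |
| 4 | 62% | 32% | 13% |

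The result swings from negligible to more than half, depending on two quantities that the protocol does not fix. A 2 µm cut-off holds a 5% rate only if SD ≤ 2/1.96 = 1.02 µm. If all the error were within-visit, that means a single-scan SD of 1.02/√(2/3) = 1.25 µm.

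**4. Can noise alone lift 20% to 50%?** Suppose 20% truly change, LiveOCT detects all of them as the section expects, and a proportion f of the other 80% is flagged in error. Then flagged = 0.20 + 0.80f:

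- f = 5% gives 24%
- f = 10% gives 28%
- f = 20% gives 36%
- f = 37.5% gives 50%

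At c = 2 µm, f = 37.5% corresponds to SD = 2.25 µm, or a single-scan SD of 2.25/√(2/3) = 2.8 µm if all the error is within-visit. The same 37.5% = (0.50 − 0.20)/0.80 is the rate of extra calls among Pentacam non-changers that the plan itself implies. It does not show that those calls are false.

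**5. Would a significance test reveal it?** The protocol names no test for this contrast, so take an exact two-sided McNemar test in 36 patients with discordance in one direction only. Six discordant patients suffice (2 × 0.5⁶ = 0.031, whereas 2 × 0.5⁵ = 0.063). With discordance of 0.80 × 0.375 = 0.30, P(Bin(36, 0.30) ≥ 6) = 98%. A small p-value would be almost certain with no extra true change. At f = 5% (discordance 0.04) the probability is 0.3%, so controlling f is what gives the comparison meaning.

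**6. What can the healthy group show?** If 0 of 20 are flagged, the one-sided 95% upper bound is 1 − 0.05^(1/20) = 13.9%.

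**The case against.** Much can be said for the plan.

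- **Control of false positives.** A reader might infer that there is none and that the result could never be told apart from noise. The documents do not support that. Triplicate scans, repeatability analyses and a healthy group would supply the data needed to set a limit, and an SAP that is not shown could use them. What remains is that the protocol does not link these data to a LiveOCT definition of change or to the 50%. The resolution argument is the protocol's own, and an SAP would not remove it.
- **Healthy-eye limits.** A reader might infer that a limit from healthy eyes would be applied to keratoconus, since 8.81 µm is smaller than 12.1 µm. Nothing in the protocol says so. The healthy group is to contribute reproducibility data, not to be its only source.
- **Illustrative inputs.** The 2 µm cut-off and every SD above are assumed, and a precise device would sit in the favourable first row. This stands. The table shows what noise could do, not what it will do.
- **Extra calls may be real.** The hypothesis is that LiveOCT finds true change below 12.1 µm. It may, and Primary outcomes asks whether newly seen changes reflect disease status. But without matched limits, the count of flagged patients cannot decide the question.
- **Primary outcome.** Objectives and Primary outcomes name image quality and added information, and 13.2 specifies no 50% against 20% test. This limits the reach of the point. Even so, 13.1 calls TCT change primary and sizes the keratoconus group on it.

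**Conclusion.** The concern holds in this form: LiveOCT change is undefined, the 50% is an unsupported assumption, and the reason given for it conflicts with the protocol's own Pentacam figures (cut-off 12.1 µm, resolution 20 µm). As written, a higher flagged proportion would not by itself show greater sensitivity.

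The size cannot be fixed from the document. Under an assumed 2 µm cut-off and normal error, false flags in stable eyes run from 5% (SD 1.0 µm) through 32% (2 µm) and 37% (2.25 µm) to 50% (3 µm). At 2.25 µm, with 20% true changers all detected, the planned 50% appears with no additional true change. It would be wrong to conclude that LiveOCT is this noisy, or that 37.5% of non-changers would be false positives.

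**What to change.** In sections 13.1 and 13.2:

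- **(a) Define LiveOCT change for each variant** as exceeding its own 95% limit for the difference between two visit means of three: 1.96 × √[2 × (s_w²/3 + s_b²)]. Estimate the within-visit SD s_w from repeat scans in keratoconus eyes, and the between-visit SD s_b from the healthy volunteers' three scheduled visits. Repeats on a device are taken in one sitting, so s_w alone would set the limit too low. Fix the limit before the keratoconus month-6 comparison.
- **(b) Compare LiveOCT and Pentacam at limits built the same way**, with a matched nominal 5% false-positive rate. Confirm that the three-measurement rule covers the Pentacam, since its 12.1 µm cut-off presumes it.
- **(c) Report the proportion of healthy volunteers beyond each device's cut-off**, with a confidence interval, noting that 0 of 20 still allows about 14%. Because the same visits feed the limit, this checks calibration and is not independent validation.
- **(d) Remove the resolution-based justification** and label the 50% an assumption.

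Cost: wording and a little more analysis, using visits and scans already scheduled. The limit will have limited precision and assumes that between-visit error in healthy eyes carries over to keratoconus, which should be stated. The detected proportion may fall below 50%.
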